
### Data analysis

Data will be analyzed according to the protocol principle. First, to compare treatments’ and teeth longevity, both Kaplan-Meier survival analysis and Log-rank test will be applied. The association between restoration longevity and caries experience or type of cavity will be evaluated using Cox Regression.

As we have a cluster-effect related to the numbers of operators of this trial and its contextual variables (such as age, work experience and technique preference), the average event rates in the two groups over the two year study period will be then modelled and compared with a “shared frailty” model. This model is an extension of the Cox proportional hazard model that includes a frailty term (a statistical expression for random effect, unrelated to the clinical concept of frailty) to take dependency of events within a contextual (correlation between different falls by the same operator) into account. All participants will be included in the model until their last time point, which means that the model will use all available data right up to the time of withdrawal or trial completion. For each outcome, we will present the hazard ratios and 95 % confidence intervals for the intervention, adjusted by operator.

The variance analysis will be used to compare groups in relation to the cost after determining data normality through the Kolmogorov-Smirnov test. Poisson analysis will be used to assess the association between the treatment group, the preference of professionals and the cost of treatments. The significance level will be set in 5 %.

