**Methods/design:**

A total of 1,214 5-to-13 year-old children with at least one single or multiple-surface dentin caries lesion in primary or permanent molars will be selected in public schools of Barueri-SP, Brazil. The participants will be randomly assigned into 2 groups: CT (caries removal with bur and restoration performed with Scotchbond™ Universal Adhesive system associated with Filtek Bulk Fill – 3 M/ESPE) and ART (Caries removal with hand instruments and restoration with high viscosity glass ionomer cement Ketac Molar Easy Mix – 3 M/ESPE). Ten untrained dentists will perform the treatment in in dental offices located at public schools. The restorations will be evaluated after 6, 12 and 24 months by an independent trained and calibrated examiner. The restoration and tooth survival, the cost-effectiveness analysis between the two groups and the operators’ preferences regarding the techniques will be also evaluated. Kaplan-Meier survival analysis and log-rank test will be applied for the restoration and tooth survival. All the average event rates in the two groups will be modelled and compared with a Cox proportional hazard shared frailty model since there is an operator-cluster effect. The significance level for all analyses will be 5 %.

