### Study design

The design of this project comprises different dentitions (primary and permanent teeth) and different surfaces (single or multiple-surface).

This is a pragmatic, two-arm, parallel group, patient-randomized trial which has 10 dentists as operators in dental offices located at public schools. The schedule of enrolment, interventions, and assessments diagram is showed in Fig. 1.

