### PRECIS (Pragmatic-Explanatory Continuum Indicator Summary) domains

#### Elegibility/Recruitment/Setting

The participants of the trial are those who would receive dental treatment in a usual care. No extra effort will be made to recruit more participants. All children that have at least one single or multiple-surface caries lesion in a primary or permanent posterior tooth and who seek for treatment in one of the participating centers are eligible for this trial.

Only the children whose parents or legal guardians signed the informed consent and who assent to be part of the study will be included in the research. All phases of this trial will be carried out in the dental clinic located at public schools. As radiographic facilities are not available in this setting, only clinical diagnosis will be used.

As this trial aims to evaluate the restoration and tooth survival, the tooth of interest should not present any associated fistula, abscess, pulp exposure, historical of spontaneous dental pain or mobility.

Even when children do not present a cooperative behavior, they will be included in this trial, as it is a common problem in pediatric dentistry clinical practice. Other variables like size of the cavity, approximal or occlusal contact and caries experience will also not be considered as exclusion criteria. All data will be recorded and further analysed to manage if there is any influence of those clinical factors on the survival rate of the restorations.

Recruitment will take place from March to November 2016. Each participant will be enrolled in the study for about 25 months: 1 month for RCT diagnosis and treatment, followed by a 24-month observational period. Details are illustrated in Fig. 1.

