### Intervention flexibility – delivery/Adherence

The intervention will be delivered and the flexibility of the trial will be similar to the usual care. The treatments will be done by the dentists of the municipality during their normal working setting.

The patient will be invited to participate of the research since they have matched the inclusion criteria. No extra encouragement to adhere to the study will be done.

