### Interventions

Atraumatic Restorative Treatment (ART) using Glass Ionomer Cement (GIC)The treatments from ART group will be performed according to the ART guidelines as described by Frencken et al. [15]. The isolation of the operating site will be done with cotton wool. The cavity will be opened with a dental hatchet and enamel cutters. Regarding the dentin caries removal, only will be removed the soft and completely demineralized dentine with hand excavators.For the dentin conditioning, will be used the first drop of 11.5 % polyacrilic acid with a microbrush during 15 s. Then, the cavity will be washed with three cottons moistened with water and dry using other three cotton pellets.After this step, the dosage (1:1 powder-liquid ratio) and hand mixing of the material will be made. The material only can be applied while it remains glossy. The GIC application will be done with a#1 spatula followed by finger pressure using petroleum jelly. In occlusal-proximal cavities, an adapted matrix with a wooden wedge must be used to provide an appropriate contour to the restoration.After the initial setting, the occlusion will be checked with articulating paper. A new layer of petroleum jelly should be applied on the surface of the restoration after removing the excess. The dentists will give instruction to the patient to not eat solid food for one hour.Conventional Treatment (CT) using Bulk Fill composite resinThe teeth in this group will be treated in a conventional way, which dentists are used to carry out followed by restoration with composite resin. As a routine program in public health center of Barueri, no rubber dam will be used.Instructions about the removal of carious tissue will be given, using a spherical carbide drill at low speed under refrigeration or using hand instruments, according to the operator preference.After the preparation of the cavity, no cavity conditioner will be applied, since the adhesive system used (Scotchbond™ Universal Adhesive - 3 M ESPE) allows the self-etch technique.The restoration will be performed using composite resin (Filtek Bulk Fill – 3 M ESPE). If the cavity size is bigger than 4 mm, two increments must be applied.For light curing, both for the adhesive system and the composite resin, the same light equipment will be used. If necessary, finishing bur will be used for adjustments.

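### The stated analysis principle reads as per-protocol, conflicts with the all-participants rule in the same section, and analysis by allocated arm is stated nowhere

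*Protocol article*

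**What the plan says.** The Data analysis section of the protocol article gives one general principle: "Data will be analyzed according to the protocol principle". The next sentence sets out the Kaplan-Meier and log-rank comparison. The section then turns to the shared-frailty Cox model, for which it says "All participants will be included in the model until their last time point" and explains that "the model will use all available data right up to the time of withdrawal or trial completion". Neither intention to treat nor analysis in the allocated arm is mentioned anywhere in the article.

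The design is described as follows: "This is a pragmatic, two-arm, parallel group, patient-randomized trial which has 10 dentists as operators". On delivery, "the flexibility of the trial will be similar to the usual care". On eligibility, "Even when children do not present a cooperative behavior, they will be included in this trial". The operators receive guidance but no training, and the Discussion states that patients, operators and evaluators cannot be blinded.

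Caries removal in the conventional treatment (CT) arm is described in two ways. The abstract has "caries removal with bur and restoration performed with" the adhesive and bulk fill composite. The Interventions section allows a drill "or using hand instruments, according to the operator preference".

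**The concern.** A per-protocol principle makes adherence a condition for being analysed. This trial is built to let delivery vary: operators of differing experience, no training, uncooperative children included, usual-care flexibility. Deviations will plausibly follow a child's behaviour or a difficult cavity, and both plausibly affect how long a restoration lasts. Teeth dropped for such reasons are not a random subset, and the operators who influence whether a deviation occurs know the allocation. The remaining teeth would no longer be protected by randomisation. The result would describe the treatments when delivered as specified, whereas the stated aim is their effectiveness in practice.

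The section also gives two inclusion rules that do not fit together: a principle that reads as excluding deviating teeth, and a model that takes in all participants. An analyst could follow either and claim to be following the article.

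**Working it through.** **1. The two rules side by side.** The opening sentence of Data analysis is general and stands directly before the Kaplan-Meier/log-rank sentence. The all-participants sentence comes later and refers to the frailty model. It settles how long each participant contributes follow-up. It does not say in which arm a tooth is counted, and it does not extend to the log-rank comparison, which is the test used for sizing (Sample description).

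**2. Does the planned size depend on the analysis set?** Inputs from Sample description and Table 1: two-sided 5%, 80% power, ART survival of 93%, 62% and 41%, differences of 15 points (single surface) and 20 points (multiple surfaces). Freedman's log-rank formula reproduces the base sizes, with HR = ln(p2)/ln(p1), events E = (1.960 + 0.842)² × ((1 + HR)/(1 − HR))², and N = E/(1 − mean survival):

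- 93% vs 78%: HR 3.424, E = 26.15, N = 26.15/0.145 = 180.3, so 181.
- 62% vs 82%: HR 0.415, E = 45.95, N = 45.95/0.28 = 164.1, so 165.
- 41% vs 61%: HR 0.554, E = 95.51, N = 95.51/0.49 = 194.9, so 195.

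Inflating by 1.4 and 1.2, with the table's rounding, gives 304 + 278 + 304 + 328 = 1,214. The inflation covers losses and operator clustering. No step refers to adherence or to an analysis set, so naming the allocated-arm set as primary leaves 1,214 as it is.

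**3. How large could the bias be?** The article gives no deviation rate, so everything here is assumption. Deviation is taken to occur in one arm only, and the survival figures are the ART rates of Table 1.

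*Fixed gap.* Let a share x of the arm deviate and survive g points less often than adherent teeth, whose survival is a. Overall survival is (1 − x)a + x(a − g) = a − xg, so dropping the deviating teeth raises apparent survival by xg. With g = 20 points:

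- x = 10%: 0.10 × 20 = 2 points.
- x = 20%: 0.20 × 20 = 4 points.

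*Failure ratio.* A 20-point gap is steep where overall survival is 93%. At x = 10%, adherent teeth would fail at 5% and deviating teeth at 25%. A milder assumption is that deviating teeth fail r times as often as adherent ones. With overall failure f, adherent failure is f/(1 + x(r − 1)), and the rise is f − f/(1 + x(r − 1)):

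| Overall survival | x = 5%, r = 1.5 | x = 20%, r = 2 |
|---|---|---|
| 93% (f = 0.07) | 0.07 − 0.07/1.025 = 0.2 points | 0.07 − 0.07/1.20 = 1.2 points |
| 62% (f = 0.38) | 0.38 − 0.38/1.025 = 0.9 points | 0.38 − 0.38/1.20 = 6.3 points |

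The 6.3-point corner corresponds to a gap of 31.7 points (68.3% against 36.7%, before rounding), wider than the 20 points assumed above; 0.20 × 31.7 = 6.3. This form is not used for the 41% stratum, because some settings are impossible there. With 5% deviating at twice the rate, adherent failure is 0.59/1.05 = 0.562, which doubles to more than 1.

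**4. The two descriptions of CT.** Under the abstract's wording, a CT tooth excavated by hand is a deviation. Under the Interventions section it is adherent. Allocated-arm analysis counts the tooth in CT either way. Only a per-protocol set changes with the reading.

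**The case against.** The strongest reply is that the sentence is loosely worded. It may mean no more than that the analysis will follow the protocol. No sentence says that deviating teeth are dropped, and the frailty model, which supplies the adjusted hazard ratios, takes all participants up to withdrawal or completion. This stands in part. A reader might infer that exclusions are settled and that randomisation will be broken; the article does not support that, and the bias arises only on the per-protocol reading. But the all-participants sentence does not state the arm and does not cover the log-rank comparison, so the conflict remains.

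A second reply is that a trial expecting similar effectiveness may have reason to look at adherent teeth. The article states no equivalence or non-inferiority margin, however, and sizes a two-tailed test of a difference. That supports a per-protocol analysis as a sensitivity analysis, not as the principle.

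A third reply is that allocated-arm analysis dilutes the contrast if teeth cross over. With one-way crossover c, holding power would need 1,214/(1 − c)² teeth: 1,264, 1,345 or 1,499 for c of 2%, 5% or 10%. No crossover rate is given. In a pragmatic trial that dilution is part of the effect being estimated.

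Two stronger readings of the CT wording should also be set aside. A reader might infer that a per-protocol set cannot be defined at all. The Interventions section states the operator's choice openly, the arms differ by restorative material under both descriptions, and the details of such a set may sit in an analysis plan that is not shown. A reader might also infer that hand excavation in CT would go unseen. The article does not say whether the treatment sheets record the excavation method, so that cannot be asserted.

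**Conclusion.** The point holds as a conflict in the text that should be resolved before analysis. The only stated principle reads as per-protocol, it does not fit the all-participants rule or the pragmatic aim, and allocated-arm analysis is stated nowhere. It governs the primary comparison in all four strata.

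On the per-protocol reading, with 10–20% of one arm deviating and a 20-point survival gap, the bias is 2–4 points, or 10–20% of the 20-point target. In the 93% strata, under the milder failure-ratio assumption, it is about 0.2–1.2 points against a target of 15. Larger values need wider gaps, as the 62% stratum shows, and similar deviation in both arms would partly cancel. None of these scenarios alone produces a difference of the planned size. But the trial's own hypothesis is that the treatments perform alike, and a few points could then decide which arm appears better.

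The mismatch over caries removal in CT is a minor, separate matter of wording that bears on a per-protocol sensitivity analysis.

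**What to change.** Replace the opening sentence of Data analysis with: *The primary analysis, including the Kaplan-Meier/log-rank comparison and the shared-frailty model, includes every randomised tooth in its allocated arm; a per-protocol analysis is a sensitivity analysis.* The tooth is the right unit to name, because the sample size is counted in teeth and the Discussion allows one child to contribute separately randomised teeth to different strata. The cost is one sentence, and the planned 1,214 teeth do not change.

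As a separate small edit, reconcile the abstract and the Interventions section on caries removal in CT, so that hand-excavated CT teeth are classified in one way in the sensitivity analysis. If the treatment sheet does not already record the method used, one tick-box would add it.

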### Sample description

Since single and multiple-surfaces cavities are going to be restored, both in primary and permanent teeth, and the difference expected between those groups are not the same, four sample size calculations were done.

The sample size calculation was performed using the website statstodo.com based on the primary outcome - treatment survival, using log-rank test in survival analysis. For the single surface, the calculation was based in an absolute difference between the survival rates of CT vs. ART of 15 % while for the multiple-surfaces, the absolute difference considered was 20 %. This involved a two-tailed test based on survival rate reported for ART [10] after 2 years of follow- up, α of 5 and power (strength) of 80 %. The sample size was increased 20 to compensate for possible losses during the study and 40 % to compensate operators-cluster effect. This gave a final sample size of 1214 teeth (described in Table 1).

**Table 1 Tab1:** Sample size calculation description

Tooth type	Surface	Survival Rate reported for ART (2 years)	Sample size	+20 % possible losses	+40 % operator-cluster effect
Permanent	Single surface	93	181	253	304
	Multiple surfaces	62	165	231	278
Primary	Single surface	93	181	253	304
	Multiple surfaces	41	195	273	328
				Total	1, 214

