### Organization intervention/Operators

The operators of this study will be 10 dentists who work in the dental offices located at the public schools of Barueri. All operators will receive only a guideline of how to prepare, restore and finalize the restoration according to the original procedures of ART [2]. Regarding the procedures in the CT group, all the dentists will receive explanations about the preparation of the cavity according to partial caries removal philosophy and also about the manufactures’ specifications of the materials used. Since it is a pragmatic clinical trial, operators with different clinical expertise will be selected and no training will be performed for both groups.

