In order to evaluate the preferences of dentists and measure a professional-centered outcome, a questionnaire composed of sixteen items will be applied [3]. It aims to evaluate factors influencing dentists’ preference of amalgam or composite for posterior dental restorations, which can influence the quality of the restorations.

The growing use of cost-effectiveness analysis (CEA) to evaluate the costs and health effects of specific interventions is dominated by studies of prospective new interventions compared to current practice [21]. The dental treatments (ART and CT) are daily performed during the normal clinical practice, but maybe with different materials (there is a large range of materials available in Brazilian market). In order to standardize the materials that will be used in this trial, we received a donation from the manufacturer. There is no conflict of interests, and the results will be published in good quality journals.

The patients of this trial will be children who study in the school where the dental office is located. Even it is not the best pragmatic way to perform the follow-up, the evaluation will be done by a single evaluator, in a school setting, in order to reduce drop-outs during the follow-up. This evaluation system is possible since we can locate the child aided by a national student’s data website [22].

Regarding our main outcome, to evaluate the survival rate of the ART and CT restorations, we chose the Roeleveld criteria [16], that allows splitting the evaluations in minor and major failure [23], therefore the survival of the tooth (in case of primary dentition) can also be calculated. The objective of a restoration is to provide the patient a condition for arresting caries lesion and avoid pulp problems or extractions. For that reason, studies should focus on the survival of the restored teeth and not remain limited to the minor failures of restoration survival [24, 25].

The ART is already well described in the literature, both in primary and permanent teeth [10, 26, 27] and well accepted by dentist due to its ease of use. In another hand, little is known about bulkfill composite resin, which can also be used as an aesthetic restoration and in one single increment. In that way, this pragmatic study will contribute to improve the knowledge about the ART and CT for restoring single or multiple surface carious lesions in primary and permanent dentition.

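### The Cox regression for caries experience names no operator term, although the plan acknowledges operator clustering and ties operators to school offices; a small, assumption-dependent optimism that is cheap to remove

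*Protocol article*

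**What the plan says.** The Data analysis section of the protocol article names two models. For prognostic factors: "The association between restoration longevity and caries experience or type of cavity will be evaluated using Cox Regression". No operator term, frailty or robust variance is mentioned there.

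The next paragraph opens by recognising clustering, "As we have a cluster-effect related to the numbers of operators of this trial", and on that ground says that "the average event rates in the two groups over the two year study period will be then modelled and compared with a “shared frailty” model". The promised output is limited in the same way: "we will present the hazard ratios and 95 % confidence intervals for the intervention, adjusted by operator". The Abstract also attaches the frailty model to the two groups.

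On the setting, the section on organisation and operators says: "The operators of this study will be 10 dentists who work in the dental offices located at the public schools of Barueri". The Discussion adds: "The patients of this trial will be children who study in the school where the dental office is located". The number of schools and the number of dentists per school are not given.

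The Sample description section inflates the sample by "40 % to compensate operators-cluster effect", applied in Table 1 to each of the four dentition-by-surface strata. The Randomization section stratifies by operator, dentition and surface. The Discussion allows one child to contribute teeth to more than one stratum and says the strata will be analysed separately.

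**The concern.** The plan adjusts for operator where randomisation within operator already balances operator between the arms. It names no adjustment where nothing provides that balance. Caries experience comes with the child, the child with the school, and the school with the dentists who work there. The operators are untrained for the trial and deliberately differ in expertise. If a dentist whose restorations fail more often happens to serve a high-caries school, an ordinary Cox model credits part of that dentist's failures to caries experience.

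Two things follow if caries experience differs between schools. The hazard ratio mixes within-operator and between-operator differences. Its standard error also treats the teeth of one operator as independent. At stake is a reported risk factor for restoration failure. The section on eligibility, recruitment and setting promises to examine whether such clinical factors influence survival, so this is a planned result.

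**Working it through.** **1. The plan's own figure.** The 40 % allowance is the only statement about the strength of clustering, so I first checked how it enters the sample size. The Freedman log-rank formula was used (two-sided 5 %, 80 % power, hazard ratio = ln S_CT / ln S_ART, N = events / (1 − mean survival)). The ART rates come from Table 1. CT rates of 78, 82, 78 and 61 % follow from the stated differences of 15 and 20 points. This gives N = 180.3, 164.1, 180.3 and 194.9, against 181, 165, 181 and 195 in Table 1. Multiplying by 1.4 and 1.2, for example 181 × 1.4 × 1.2 = 304.1, reproduces the final column, and 304 + 278 + 304 + 328 = 1,214. The 40 % is therefore a design effect of 1.4 within each stratum.

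**2. Implied intraclass correlation (ICC) of failure by operator.** With m teeth per operator, design effect D = 1 + (m − 1) × ICC.
- Final stratum sizes: 1,214 / 4 / 10 = 30.35 teeth per operator, so ICC = 0.4 / 29.35 = 0.014.
- An ICC of 0.022 corresponds to m = 1 + 0.4 / 0.022 = 19.2, close to the uninflated Table 1 sizes (195 / 10 = 19.5).

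The range used is 0.014 to 0.022.

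**3. Effect on a covariate.** Let r be the share of the covariate's variance that lies between operators. When operator is omitted, the variance is understated by the factor V = 1 + (D − 1) × r. The true error rate of a nominal 5 % test is 2 × (1 − Φ(1.96 / √V)). The document gives no r; 0.05, 0.10 and 0.20 are assumptions.

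| Setting | D | r = 0 | r = 0.05 | r = 0.10 | r = 0.20 |
|---|---|---|---|---|---|
| One stratum, plan's allowance | 1.40 | 5.0 % | 5.2 % | 5.5 % | 5.9 % |
| All 1,214 teeth, ICC 0.014 | 1 + 120.4 × 0.014 = 2.69 | 5.0 % | 6.0 % | 7.0 % | 9.0 % |
| All 1,214 teeth, ICC 0.022 | 1 + 120.4 × 0.022 = 3.65 | 5.0 % | 6.6 % | 8.1 % | 11.3 % |

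In the first row the standard error is 1 %, 2 % and 4 % too small. The lower rows use 1,214 / 10 = 121.4 teeth per operator.

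**4. Check by simulation.** The design had 10 operators, lognormal operator effects, exponential times, 70 % overall survival, no true covariate effect and 2,500 runs. Ordinary Cox on 1,214 teeth rejected in 6.1, 6.8 and 9.0 % of runs with an operator SD of 0.22, and in 6.4, 8.2 and 11.5 % with 0.27, in line with the formula. The same SDs run stratum by stratum gave 5 to 7 %. A 400-run check with operator as a fixed effect gave 4 to 6 %.

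**5. Cavity type.** Both surface types are planned within every operator, since surface and operator are both stratification factors. Its r is then near zero and V near 1. When strata are pooled to compare surfaces, the dependence that the document itself describes is several teeth from one child.

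**6. What the arithmetic leaves out.** Steps 3 and 4 assume that operator quality is unrelated to the school's caries level except by chance. A systematic link would bias the hazard ratio itself. The document gives nothing from which to size that bias.

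**The case against.** The strongest reply is that this rests on one sentence about an exploratory analysis in a condensed article. Covariate sets and variance estimators are commonly left to a statistical analysis plan, the frailty model is described as an extension of Cox, and operator is nowhere expressly excluded. Part of this stands: the point is minor and concerns neither the primary outcome nor a listed secondary outcome. It does not dispose of the point. The section assigns one model to the covariates and another to the arms, and limits operator adjustment to the intervention's hazard ratio.

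Four stronger readings are tempting and are not supported:
- A reader might infer that operator and school coincide. The document links them but does not state one dentist per school.
- A reader might infer that the intervals are certainly too narrow. That requires caries experience to differ between operators. With r = 0 an ordinary Cox model keeps its nominal level.
- A reader might take 9 to 11 % as the size implied by the plan's 40 %. That figure needs all strata pooled and a 20 % between-operator share. The Discussion describes separate analyses by dentition and surface. If 1.4 were instead the pooled design effect (ICC 0.4 / 120.4 = 0.003), the pooled rate would again be 5.2 to 5.9 %.
- A reader might extend the argument to cavity type. It hardly reaches that factor unless case mix differs by operator.

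**Conclusion.** The point holds in limited form. The plan names an operator-adjusted model for the arm comparison and an ordinary Cox regression for caries experience, the association more exposed to operator differences. If caries experience differs between schools, its hazard ratio can be confounded with operator and its interval is somewhat too narrow. For between-operator shares of 5 to 20 %, the false-positive rate is about 5 to 6 % within one stratum at the plan's allowance, and about 6 to 11 % if the same ICC applies to all 1,214 teeth pooled. The shares, the pooling and the carrying over of the ICC are assumptions. The treatment comparison is not affected.

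**What to change.** State in the Data analysis section that associations with caries experience and type of cavity will be estimated in an operator-adjusted Cox model that includes treatment arm. Stratifying by operator, or entering operator as a fixed effect, is preferable to a frailty term alone, because the association is then estimated within operator and between-operator confounding is removed. Where dentition or surface strata are pooled, also allow for several teeth from the same child, for example with a child-clustered robust variance; operator adjustment does not deal with that.

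The cost is a sentence or two in the plan and slightly wider intervals. No new data are needed, because operator is already recorded as a stratification factor.

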### Participant selection

The criteria for caries presence will be the World Health Organization [11] and the DMFT and dmft will be recorded [12]. The biofilm evaluation according to the criteria proposed by Löe (1972) [13] and the gingival health [14] will be held before the restoration (baseline).

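### The ART versus CT hazard ratio is adjusted for operator only: valid and powered as planned, but it forgoes a modest gain from baseline values the trial already has

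*Protocol article*

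**What the plan says.** The Data analysis section plans Kaplan-Meier curves and a log-rank test, then a Cox model with shared frailty for operator. It names the adjustment: "For each outcome, we will present the hazard ratios and 95 % confidence intervals for the intervention, adjusted by operator". A Cox regression of restoration longevity on caries experience or type of cavity appears as a separate item; the text does not say whether treatment is in that model.

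On what is measured, Participant selection says "The criteria for caries presence will be the World Health Organization [11] and the DMFT and dmft will be recorded [12", and adds plaque and gingival scores taken before the restoration. The Abstract gives the age range as 5 to 13 years. The Elegibility/Recruitment/Setting section admits children whatever their cooperation, cavity size, contacts or caries experience, and says of these: "All data will be recorded and further analysed to manage if there is any influence of those clinical factors on the survival rate".

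Randomisation is stratified by operator, dentition and surface. The Discussion says the analyses are run separately by dentition and surface. The sample size is "based on the primary outcome - treatment survival, using log-rank test in survival analysis", with "α of 5 and power (strength) of 80" %.

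**The concern.** Eligibility is deliberately broad, so teeth within one stratum will differ in caries experience, patient age and cavity size. None of these is a randomisation factor and none is in the treatment model. If they predict restoration failure, a model that includes them has a better chance of detecting a given difference between ART and CT. Caries experience and age need no new data collection.

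There is also a pre-specification argument. The evaluator cannot be blinded, and clinical factors are to be analysed further. Naming the covariates now removes any later choice between an adjusted and an unadjusted hazard ratio.

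**Working it through.** **1. The plan's own sample sizes.** Inputs, all from Sample description and Table 1: two-sided alpha 5 %, power 80 %; 2-year ART survival 93, 62, 93 and 41 %; "absolute difference between the survival rates of CT vs. ART of 15" % for single surfaces, and "for the multiple-surfaces, the absolute difference considered was 20" % for multiple surfaces. Freedman's log-rank formula: HR = ln(p2)/ln(p1); events = (1.96 + 0.84)² × [(1 + HR)/(1 − HR)]²; N = events / mean failure probability, both arms together.

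- Single surface, 93 vs 78 %: HR 3.42, 26.1 events, divided by 0.145 gives N = 181.
- Permanent multiple, 62 vs 82 %: HR 0.415, 45.9 events, divided by 0.28 gives N = 165.
- Primary multiple, 41 vs 61 %: HR 0.554, 95.5 events, divided by 0.49 gives N = 195.

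These match Table 1. Multiplying by 1.4 and 1.2 and rounding up gives 304, 278, 304 and 328, total 1,214. No covariate enters, so the planned power is that of an unadjusted test.

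**2. Gain from adjustment.** Prognostic strength is not in the documents. Assumption: one standardised baseline score standing for all covariates together, with a hazard ratio per SD of 1.25, 1.5 or 2.0. Event times were simulated so that marginal 24-month survival equals the design values, at the pre-inflation N. Cox models were fitted without and with the score, 1,500 runs per scenario (Monte Carlo standard error of each power figure about 1 point: √(0.82 × 0.18/1500) = 0.010).

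| HR per SD | Single 93/78, N = 181 | Permanent multiple 62/82, N = 165 | Primary multiple 41/61, N = 195 |
|---|---|---|---|
| 1.25 | 82.1 to 82.0 % | 82.4 to 83.0 % | 81.4 to 82.1 % |
| 1.5 | 80.4 to 81.5 % | 82.3 to 83.9 % | 81.7 to 85.3 % |
| 2.0 | 80.4 to 83.7 % | 81.6 to 86.9 % | 82.5 to 90.7 % |

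Differences: −0.1, 0.6 and 0.7 points at 1.25; 1.1, 1.6 and 3.6 at 1.5; 3.3, 5.3 and 8.2 at 2.0. Type I error without adjustment was 2.9 to 5.0 % in these scenarios.

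A second simulation was nearer to the planned setting: 10 operators, gamma frailty variance 0.1 (assumed), failures seen at 6, 12 and 24 months, operator-stratified Cox. For the multiple-surface strata, power with operator only, then with operator plus score, was:

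- log HR 0.4 per SD (HR about 1.5): 80 to 82 % permanent, 80 to 84 % primary.
- log HR 0.7 (HR about 2.0): 83 to 88 % and 80 to 87 %.

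Direction and size agree.

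**3. Chance imbalance.** With n analysed teeth in two equal arms, the standardised mean difference of a covariate has SD 2/√n. In one trial in 20 imbalance shifts the unadjusted HR by more than exp(1.96 × 2/√n × log HR per SD). After 20 % losses n = 278 × 0.8 = 222 and 328 × 0.8 = 262. At 0.4 per SD: exp(1.96 × 0.134 × 0.4) = 1.11 and exp(1.96 × 0.124 × 0.4) = 1.10. At 0.7 per SD: 1.20 and 1.18.

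**4. Room for covariates.** Single surface: 304 × 0.8 = 243 teeth; 243 × 0.145 = 35 events.

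**The case against.** The strongest reply is that nothing here is wrong. Analysis within dentition and surface, with operator in the model, accounts for every stratification factor. The trial is sized for an unadjusted test. A fuller covariate list often sits in a statistical analysis plan, which is not shown. The first two points stand. The third does not remove the point, because the article states the adjustment rather than leaving it open.

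A reader might infer that the primary comparison gives up planned power and is left unprotected against chance imbalance. The documents do not support this. Table 1 is reproduced without covariates, and the test's error rate and the confidence interval already allow for chance imbalance.

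A reader might also take the move of the Cox hazard ratio towards 1, when a prognostic factor is left out, as bias. It is a different target, averaged over that factor, and legitimate for a pragmatic trial. For the same reason the gain from adjustment comes mainly from a conditional hazard ratio further from 1, and not from a narrower interval around the same one. The shared-frailty hazard ratio is already conditional on operator, so adding covariates extends the same kind of estimate.

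Three further readings go too far. The plan does not say that it expects clinical factors to affect survival; it asks whether they do. It does not ignore them, since a Cox regression on caries experience and type of cavity is planned. And nowhere does it say when cavity size is recorded, so that it is a baseline value cannot be assumed.

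The gains above are at the pre-inflation N. If the operator term absorbs the clustering, the inflated sizes leave the multiple-surface strata near 90 % power (2.80 × √(222/165) − 1.96 = 1.29, normal probability 0.90; 262/195 gives the same). The room for gain is then smaller.

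**Conclusion.** The operator-only shared-frailty hazard ratio is valid and, on the plan's own assumptions, reaches its 80 % power. It forgoes a modest amount of power that caries experience and age could supply: about 0 to 4 points if the covariates jointly carry a hazard ratio of 1.25 to 1.5 per SD, and about 3 to 8 points at 2.0. The least gain is in the single-surface strata, which hold 608 of the 1,214 teeth. The direction is secure if the covariates are prognostic. The size is not, because it rests wholly on assumed prognostic strengths. This is an improvement in efficiency and pre-specification, not the repair of an error.

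**What to change.** In the Data analysis section, state that in each of the four dentition-by-surface strata the primary ART versus CT hazard ratio comes from the shared-frailty Cox model, with operator as the frailty term and baseline caries experience and age as covariates. Say which caries index is used in which stratum (dmft, DMFT or both). Report the operator-only hazard ratio as supporting. Add cavity size only if it is recorded before excavation, since preparation with bur or hand instruments can change it. Say also whether treatment is in the planned Cox regression on caries experience and type of cavity.

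The cost is a change of wording, best dated before outcome data are examined because recruitment is already under way. There are two small downsides. With about 35 events expected per single-surface stratum, covariates must stay at two or three. And the primary hazard ratio becomes conditional on them, which the report should say.
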